### Recruitment and consent

The patients will be screened by experienced neurosurgeons in each center according to the inclusion and exclusion criteria. The surgeons should help patients understand the risks of two treatment strategies and written consent will be obtained from them. If the patients screened for this trial are unconscious or mentally impaired due to the stroke at admission, informed consent of their relatives will be obtained instead and consent of the patients will be obtained if they regain consciousness after treatment. If patients are incapacitated and their relatives cannot be located, these people will not be included in this trial. Any individual with a direct relationship to the researchers, such as close relatives or staff of the hospital, will not be included.

### Randomization

We adopt a central randomization method based on the mobile client randomization tool “Randomization Allocation Tool” (RAT) to achieve random assignment of patients into two groups at a 1:1 ratio. If the subject is qualified for the trial and signs the informed consent form, the investigator authorized by each center can input the relevant information (e.g., age, gender, the bleeding volume, scores of Graeb scale, and GCS) of the corresponding subject in the mobile phone client. After the administrator approves the confirmation, the assigned group is immediately fed back to the researcher’s mobile phone, and the researcher will perform the prescribed surgical treatment according to the specified group. Possible facts that may impact the outcomes of the patients, such as age, gender, scores of Graeb scale, and GCS, will be considered by a minimization random allocation system.

### Treatment

#### Endoscopic group

The patient in the endoscopic group will be placed in the supine position and under general anesthesia. Endoscopy is performed using a rigid endoscope (Karl Storz, German). The side with more hemorrhage will be taken as the surgical side and a transverse incision of about 3 cm in length will be performed 1–2 cm in front of the coronal suture, 2–3 cm beside the midline. Then, a bone window with a diameter of 2–3 cm will be made and we will cross-incise the dura mater. Next, the surgeons insert the endoport (Vycor Medical, USA) into the lateral ventricle, which will become the endoscopic work channel. The hematoma will be removed by a technique using irrigation and aspiration. After exposing the choroid plexus of the lateral ventricle, surgeons should strive to clear the hematoma in the third ventricle through the interventricular orifice. At the same time, the blood clots will be removed with grasping forceps and if there is bleeding, bipolar coagulation can be used to stop bleeding. During the operation, the veins, choroid plexus, and ventricular wall should be carefully protected and blood clots that are closely adhering to the choroid plexus are not required to be completely removed. The third ventriculostomy and pellucid septostomy should be performed if possible. The ventricular drainage catheter will be placed on the surgical side. The dura and skin will be closed in a routine manner. An immediate postoperative CT scan will be performed to assess the residual hematoma. After 6 h postoperatively, we will administer 20,000 U urokinase with 5 ml saline every 8 h through the catheter, and the catheter will be clamped for 1 h to allow drug–clot interaction and then reopened to allow for gravitational drainage. Subsequent CT scans will be done for any safety concern or every 24 h. Administration of urokinase will be stopped when the CT scans show that the circulation of cerebrospinal fluid is unobstructed. When CT scans show that the intracerebral hematoma is significantly reduced and the circulation of cerebrospinal fluid is unobstructed, the catheter shall be clamped for 24 h before removing the catheter. If there is no acute intracranial pressure increase, the catheter can be removed then.

#### EVD group

The patient in the EVD group will be placed in the supine position and under general anesthesia. Bilateral external ventricular drainage will be performed regularly and unilateral drainage will be performed only when the other lateral ventricular has little hematoma and the circulation of cerebrospinal fluid is unobstructed. Surgeons usually select the point 1–2 cm before the coronal suture of the bleeding side and 2–3 cm next to the midline as the puncture point and puncture inwardly along the plane of the puncture point and the line of the ear. The surgeons will use a soft catheter with a guide needle to puncture in depth of about 5 cm and then pull out the guide needle. The next step is to fix the drainage catheter and suture the scalp incision. Postoperative CT will be done immediately to confirm the positioning of the soft catheter and stability of the hematoma. After at least 6 h postoperatively, we will administer 20,000 U urokinase with 5 ml saline every 8 h, and the catheter will be clamped for 1 h to allow drug–clot interaction and then reopened to allow for gravitational drainage. Subsequent CT scans will be done for any safety concern or every 24 h. Administration of urokinase will be stopped when the CT scans show that the circulation of cerebrospinal fluid is unobstructed. When CT scans show that the intracerebral hematoma is significantly reduced and the circulation of cerebrospinal fluid is unobstructed, the catheter shall be clamped for 24 h before removing the catheter. If there is no acute intracranial pressure increase, the catheter can be removed then.

### Outcome measures

The primary outcome is the survival rate of patients at 12 months after surgery.

In addition, secondary outcome measures include treatment-related morbidity, as evaluated by the following items:
Overall survival (time to death after surgery).Modified Rankin score (preoperational, 1 month, 3 months, 6 months, 12 months).Proportion of patients who need ventricular-peritoneal shunt after surgery (1 month, 3 months, 6 months, 12 months).Incidence of postoperative hydrocephalus (1 month, 3 months, 6 months, 12 months).Postoperative intracranial infection rate (1 month, 3 months, 6 months, 12 months).Hospital length of stay.Hospitalization expenses (costs spent during treatment for IVH in hospital).

The relevant data will be collected by two data entry staff independently.

The study will include a follow-up period of 12 months. Patients will stay in the hospital for at least 2 weeks postoperatively to complete the required assessments (e.g., GSC and Graeb scale, blood and urine tests, brain CT and MRI, CTA/MRA/MRV/DSA) which are shown in Table 1. The final study follow-up is scheduled at 12 months after surgery. The patients will be reminded to return to the hospital by phone calls at 1 month, 3 months, 6 months, and 12 months after surgery to perform associated clinical examinations and tests (e.g., blood and urine tests, brain CT and MRI, modified Rankin Scale, records of the complications and survival state).

**Table 1 Tab1:** Enrollment and assessments in the trial

Item	Screening period	Follow-up							
		Operation day	1 day after the operation	7 days after the operation	2 weeks after the operation	1 month after the operation	3 months after the operation	6 months after the operation	12 months after operation
**Informed consent**	X								
**Collect demographic data**	X								
**Collect medical history**	X								
**Physical examination**	X	X	X	X	X	X	X	X	X
**Routine blood examination**	X	X	X	X	X	X	X	X	X
**Blood biochemical examination**	X	X	X	X	X	X	X	X	X
**Routine urine test**	X		X	X	X	X	X	X	X
**Brain CT scan**	X	X	X	X	X	X	X	X	X
**Brain MRI**	X					X	X	X	X
**CTA/MRA/MRV/DSA (choose 1 or 2 items)**	X								
**HIV, HBV, HCV screening**	X								
**Graeb score**	X	X	X	X	X	X			
**Glasgow Coma Scale**	X	X	X	X	X	X			
**Inclusion/exclusion criteria**	X								
**Randomization**	X								
**Survival rate at 12 months postoperatively**									X
**Modified Rankin Scale**		X	X	X	X	X	X	X	X
**Postoperative patient survival (OS)**		X	X	X	X	X	X	X	X
**Postoperative complications**		X	X	X	X	X	X	X	X

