### Inclusion and exclusion criteria

#### Inclusion criteria

Patients of either sex, 18–70 years of age.Clinical manifestation as moderate to severe IVH, such as severe headache, hemiplegia, aphasia, or unconsciousness.Disease onset within 24 h.Graeb scale > 4.Glasgow Coma Scale < 13.CT scan showing the existence of hemorrhage breaking into the ventricles or primary intraventricular hemorrhage, and the bleeding volume being larger than 50% of the volume of the lateral ventricle.

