### Statistical analysis

All statistical analyses in the study will be carried out by an analyst who is blinded as to the allocated intervention. The primary efficacy will be compared by an intention-to-treat analysis including all randomized patients.

Regarding the primary outcome (the 12-month survival rate), the Cox regression model method will be used to calculate the hazards ratio and the 95% confidence interval (CI). The non-inferiority of the new surgical method and the conventional method is determined according to whether the upper limit of the 95% CI of the HR is less than 1.3. If the upper limit of the 95% CI is less than 1.3, the non-inferiority is accepted. Otherwise, a non-inferiority conclusion cannot be reached.

For the secondary outcomes, the OS curves will be estimated using the Kaplan–Meier method. Continuous variables will be assessed for normality and equality of variances between groups. Discrete variables will be summarized by frequencies/proportions. For continuous variables, analysis of variance and/or regression will be used, where appropriate (hospital length of stay, hospitalization expenses). The comparison of the two groups with respect to frequencies/proportions will be performed using the *χ*^2^ test and, if necessary, Fisher’s test (proportion of patients who need ventricular-peritoneal shunt after surgery, incidence of postoperative hydrocephalus, postoperative intracranial infection rate). The ranked data of the two groups will be compared using the Wilcoxon rank-sum test (mRS).

At the annual monitoring meeting of the Data and Safety Monitoring Board, the treatment effectiveness (the 12-month survival rate) will be compared between the two groups. If one group has significantly more hazards than the other one (upper limit of the 95% CI of the hazards ratio is more than 1.3), the trial will be terminated.

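### Survival is timed from surgery but analysed in all randomised patients, so a patient who never reaches the operation has no time origin; the two statements need reconciling

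*Protocol article*

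**What the plan says.** The clock is fixed at surgery wherever the protocol article mentions survival. Under Outcome measures, "The primary outcome is the survival rate of patients at 12 months after surgery". The first secondary outcome is "Overall survival (time to death after surgery"). On visits, "The final study follow-up is scheduled at 12 months after surgery". Table 1 has a row for the 12-month postoperative survival rate and another for "Postoperative patient survival (OS"), the latter first recorded on the operation day. The Abstract words the primary objective in the same way.

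The analysis set is fixed at randomisation. Under Statistical analysis, "The primary efficacy will be compared by an intention-to-treat analysis including all randomized patients". For that comparison "the Cox regression model method will be used to calculate the hazards ratio and the 95% confidence interval (CI"), with non-inferiority accepted if the upper limit is below 1.3.

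Randomisation comes first. Table 1 places it in the screening column, and under Randomization, once the allocation is returned, "the researcher will perform the prescribed surgical treatment according to the specified group". No section gives the interval between allocation and surgery. No section gives a start time for a patient who is randomised and not operated on.

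**The concern.** These are acutely ill patients: the Inclusion criteria require "Disease onset within 24 h", a Glasgow Coma Scale below 13 and a Graeb score above 4, and the Sample size section assumes 30% mortality at one year. It is plausible, though the article gives no figure, that a few will die between allocation and operation or will not have the assigned operation at all.

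Such a patient belongs to the analysis set but has no time zero under the endpoint definition. The analyst must either leave the patient out, which contradicts the intention-to-treat statement, or use a time origin that the article does not define. Leaving patients out would condition the comparison on surviving to surgery, an event after randomisation. The arm that loses more patients before surgery would then shed more of its earliest deaths and look better than it is. In a non-inferiority test, that could move the result either way across the margin.

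**Working it through.** **Side by side.** Clock: surgery (Abstract, Outcome measures, Table 1). Analysis set: all randomised (Statistical analysis). Order: randomisation, then surgery (Randomization, Table 1). The three fit together only if every randomised patient is operated on.

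**Inputs from the document.** 478 patients per group, 956 in total; 5% dropout; 12-month mortality 30% in both arms; HR margin 1.3, so ln 1.3 = 0.262. The article gives no figure for pre-operative deaths or for time to surgery, so there is no figure of its own to reproduce on this point. The 956 is taken as given; whether it follows from its stated inputs is a separate question.

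**Assumption.** A fraction x of one arm dies before surgery, with x = 1% (0.01 × 478, about 5 patients) or 2% (about 10). The true 12-month mortality from randomisation is 30% in both arms, so the true HR is 1.

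**Effect if those deaths were omitted.** Survival in the affected arm becomes 0.70/(1 − x). Under proportional hazards, HR = ln(survival, endoscopic)/ln(survival, EVD).

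- No omission: −ln 0.70 = 0.3567.
- x = 1%: mortality 0.29/0.99 = 29.3%; −ln(0.70/0.99) = 0.3466.
- x = 2%: mortality 0.28/0.98 = 28.6%; −ln(0.70/0.98) = 0.3365.

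| Omitted deaths | HR at 1% | HR at 2% |
|---|---|---|
| Endoscopic arm only | 0.3466/0.3567 = 0.97 | 0.3365/0.3567 = 0.94 |
| EVD arm only | 0.3567/0.3466 = 1.03 | 0.3567/0.3365 = 1.06 |
| Both arms equally | 1.00 | 1.00 |

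On the log scale the one-sided shifts are 0.029 and 0.058, which are 11% and 22% of 0.262.

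**Slack in the test.** Evaluable patients: 956 × 0.95 = 908. Deaths: 908 × 0.30 = 272. SE(log HR) ≈ √(4/272) = 0.121. To pass, the estimated HR must be below exp(0.262 − 1.96 × 0.121), about 1.02. The shifts are about a quarter (0.029/0.121) and a half (0.058/0.121) of one standard error.

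**Error rate at the margin.** Cox trials were simulated with 454 evaluable patients per arm and 6,000 runs per scenario, with the true HR from randomisation at about 1.3. The share of trials that wrongly declared non-inferiority was:

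| Pre-operative deaths, endoscopic vs EVD | Counted | Omitted |
|---|---|---|
| 0% vs 0% | 2.7% | 2.7% |
| 1% vs 0% | 2.8% | 4.8% |
| 2% vs 0% | 2.6% | 7.2% |
| 3% vs 1% | 2.9% | 6.2% |
| 2% vs 2% | 2.6% | 1.9% |
| 0% vs 2% | 2.8% | 0.8% |

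Counting the deaths from randomisation holds the rate near 2.5% in every scenario. Omitting them raises or lowers it according to the arm that loses more.

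**The case against.** The strongest reply is that the analysis statement already settles the matter. It includes everyone randomised, so a death before surgery is a death. For a 12-month survival rate, such a patient is simply a non-survivor. In a Cox model, which uses the order of events, the patient can be entered as the earliest death with everyone at risk, and the HR is practically the same as with a clock from randomisation. On that reading the bias computed above never arises, and what is left is a handling rule that a statistical analysis plan could supply.

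Much of this stands. A reader might infer that the trial will exclude pre-operative deaths; nothing in the article says so, and the intention-to-treat sentence points the other way. A reader might also infer that the bias favours the endoscopic arm because that operation takes longer to arrange. No section gives a delay for either arm, both procedures are done under general anaesthesia, and allocation is returned at once, which fits a short interval without proving one. The direction is unknown.

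The reply does not remove the conflict. Entering a pre-operative death as the earliest event already departs from a clock that starts at surgery. It also does nothing for a patient who is never operated on and survives, for whom a date 12 months after surgery does not exist. And this is not a detail left for later: the article fixes the time origin, so an analysis plan that started at randomisation would contradict the stated endpoint.

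**Conclusion.** The point holds as an inconsistency between endpoint definition and analysis set. Survival is timed from surgery, the primary analysis covers all randomised patients, and anyone who does not reach surgery has no time origin.

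The bias is conditional. It needs pre-operative losses of some size, an imbalance between arms, and omission of those patients contrary to the stated analysis set. The 1–2% one-arm losses, and the 0–3% used in the simulation, are assumptions, and the number affected may be small if surgery follows allocation quickly. Within those assumptions the HR could be moved to between about 0.94 and 1.06 when the truth is 1.00, with no shift if losses are equal. That matters because, with about 272 deaths, the estimate must be about 1.02 or lower to pass. The document supports neither a claim that the plan breaks intention-to-treat nor a claim that it is tilted towards non-inferiority. It should be corrected before outcomes are known, particularly as the treatment arms cannot be blinded.

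**What to change.** Define the primary outcome as death from any cause within 12 months of randomisation. Start the clock at randomisation for the Cox model, for overall survival and for the Kaplan–Meier curves. Include every randomised patient whether or not operated on. Keep times from surgery as descriptive. Bring the Abstract, Outcome measures and the survival rows of Table 1 into line with Statistical analysis.

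The planned sample size does not change because of this. The cost is small but not purely one of wording. The Randomization section describes the data entered and the return of the allocation but does not say that the date and time are stored, so their capture should be confirmed. Because the visits in Table 1 are anchored to the operation, 12-month vital status must also be obtained separately for randomised patients who are not operated on.

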### Blinding

Due to the different surgical strategies of the two groups, no data could be collected blinded. The statistical analysis will be performed by specialized persons who are blinded as to the allocated intervention.

### Data collection and data management

Case report forms (CRFs) and clinical reports will be collected as the main data source in this trial. According to the regulations, two data entry staff will input the contents into the database independently as double copies. The database will be locked and transferred to the quality control group through the data management network after a data consistency check and a data quality audit are completed.

### Sample size

The sample size calculation results in a requirement of 956 patients. For EVD, the mortality rate is 23% in a meta-analysis of 4 randomized and 8 observational studies of patients with IVH [11]. In the CLEAR III trial, the mortality rate of the IVH patients treated with EVD plus rtPA is 18% at 180 days [13]. And the reported mortality rate of IVH patients treated with endoscopic surgery at 1 year ranges from 10 to 30% [1, 19, 20]. Based on previous studies and our own experience, we assume a 1-year overall survival rate of 70% (mortality rate of 30%) in both the reference group and the new surgical group. We plan for the trial to show non-inferiority of a new surgical method to the conventional method with a hazard ratio (HR) margin of 1.3 [21, 22]. The principle of the sample size calculation of a non-inferiority trial is different from that of a superiority trial where you want to demonstrate that one treatment or intervention is better than another. In the context of non-inferiority trials, the non-inferiority limit is used to calculate the sample size. The percentage for those on the experimental treatment is no worse than the percentage for those on the control treatment by the non-inferiority limit. In our study, the non-inferiority limit of the hazards ratio (HR) is set to 1.3. Accounting for a potential dropout rate of 5%, 956 patients (478 in each group) are needed to be enrolled, which ensured a power of 80%.

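### The stated 80% power is wrong: 956 patients followed for 12 months at 30% mortality give about 272 deaths and 58% power for the hazard ratio margin of 1.3, where 80% needs about 456 deaths.

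*Protocol article*

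**What the plan says.** The inputs to the power claim are all in the protocol article.

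- **Sample size:** "we assume a 1-year overall survival rate of 70% (mortality rate of 30%) in both the reference group and the new surgical group", so the true hazard ratio is taken as 1.
- **Sample size:** "the non-inferiority limit of the hazards ratio (HR) is set to 1.3".
- **Sample size:** after allowing for 5% dropout, "956 patients (478 in each group) are needed to be enrolled, which ensured a power of 80" per cent.
- **Statistical analysis:** the hazard ratio comes from a Cox model, and non-inferiority is judged by "whether the upper limit of the 95% CI of the HR is less than 1.3".
- **Outcome measures:** the primary outcome is survival at 12 months, and "The final study follow-up is scheduled at 12 months after surgery".
- **Study design:** allocation is 1:1.

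The Sample size section gives no significance level for the calculation, no required number of deaths, and no assumption about accrual or about follow-up beyond 12 months.

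**The concern.** The precision of a Cox hazard ratio is set by the number of deaths, so a hazard ratio margin first fixes a number of deaths and only then a number of patients. A margin of 1.3 is narrow and needs several hundred deaths. With 30% mortality and follow-up closed at 12 months, 956 patients look too few to supply them.

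The sample size rests on this figure. If power is well below 80%, the trial may randomise 956 critically ill patients and still be inconclusive when the two operations are equally good. The ethics committee, the Data and Safety Monitoring Board and readers would all be relying on an assurance that the design does not provide.

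**Working it through.** **Inputs.** Margin 1.3 (ln 1.3 = 0.26236), true hazard ratio 1, 30% mortality in both arms, 5% dropout and N = 956 (Sample size); upper limit of a 95% interval, hence one-sided 0.025 (Statistical analysis); 1:1 allocation (Study design); follow-up fixed at 12 months (Outcome measures). The normal quantiles are 1.960 for one-sided 0.025 and 0.842 for 80% power.

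**1. Attempt to reproduce 956.** Deaths required, by Schoenfeld's formula:

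d = 4 × (1.960 + 0.842)² / (0.26236)² = 456.1, or 457 rounded up. Freedman's formula gives 462.

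Evaluable patients at 30% mortality: 457 / 0.30 = 1,524. With 5% dropout: 1,524 / 0.95, about 1,604. The stated 956 is not reproduced.

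**2. Power of the trial as planned.**

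Expected deaths = 956 × 0.95 × 0.30 = 272.5.

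Power = Φ(0.26236 × √272.5 / 2 − 1.960) = Φ(0.205) = 58.1%.

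A simulation of the Cox analysis (454 patients per arm, exponential survival, censoring at 12 months, 4,000 runs) gave 58.7%, with a mean of 272.8 deaths.

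**3. More favourable readings within the 12-month design.**

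| Reading | Deaths | Power with 956 patients |
|---|---|---|
| As stated | 272 | 58.1% |
| Dropout costs no deaths | 287 | 60.3% |
| Death rate averaged over hazard ratios 1 and 1.3 | 305 | 62.9% |
| One-sided 0.05 (conflicts with the 95% limit rule) | 272 | 69.9% |

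None reaches 80%. At one-sided 0.05, 80% power would still need 360 deaths and 1,264 patients. A non-inferiority test on 12-month proportions at one-sided 0.025 does not return 956 either. It needs 1,377 patients if the margin is converted to 7.1 percentage points (0.70 − 0.70^1.3), and 857 if it is taken as 9 points (30% × 0.3).

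**4. What would have to be true.** With 956 × 0.95 = 908 evaluable patients, 80% power needs 456.1 / 908.2 = 50.2% of them to die, against the assumed 30%.

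**5. What 272 deaths can show.** The largest observed hazard ratio that still meets the criterion is exp(0.26236 − 1.960 × 2/√272.5) = 1.025. With 272 deaths and a true hazard ratio of 1, 80% power is available only for a margin of exp(2.802 × 2/√272.5) = 1.40.

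**6. Sensitivity to mortality (not the plan's assumption).** The Sample size section also cites mortality of 23%, and of 18% at 180 days, for drainage-treated patients. Used as 12-month rates in both arms, they give 208.9 deaths and 47% power, and 163.5 deaths and 39% power. The 18% is not a 12-month figure and no time point is given for the 23%, so these show only the direction and rough size of the effect.

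**The case against.** The strongest defence is that 956 came from a conventional calculation with staggered entry and follow-up to a common closing date. The Trial status section describes a recruitment period followed by 12 months, and the assumptions could sit in a full protocol that the article condenses. With constant-hazard survival of 70% per year, 2 years of accrual and everyone followed to year 3, the probability of death is 0.50. The requirement is then 457 / 0.50, about 915 patients, or 963 with dropout, which is close to 956.

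This may explain where the number came from, but it does not make the claim true of this trial. It counts deaths after month 12, while the primary outcome and the final visit are both at 12 months. It also needs 2 years of accrual, whereas Trial status has recruitment from 2020 to September 2023 and about 4 years in all. Three years of accrual plus one year of follow-up gives 844, not 956.

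Another route also lands nearby: using the total number of deaths as the number of patients per arm (456.1 × 1.05 = 478.9). The documents cannot distinguish the two, so the origin of 956 remains unknown and the conclusion does not depend on it.

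Two further objections stand in part. Vital status may still be known for patients who drop out, so 58–60% is a fairer statement than 58% alone. And the eligibility criteria (Graeb above 4, Glasgow Coma Scale below 13) may select patients with higher mortality than the cited studies, so the 39–47% range is sensitivity only.

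**Conclusion.** The concern holds. On the plan's own inputs, 956 patients give about 272 deaths and 58% power (287 deaths and 60% if dropout costs none), not 80%. The shortfall against the 456 deaths needed is about 184, or 40%. If the operations are equal, the chance of failing to show non-inferiority is about 40–42%, roughly twice the implied 20%.

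This rests on a true hazard ratio of 1, 30% mortality in both arms, follow-up ending at 12 months, and the one-sided 0.025 level implied by the 95% limit. All four are stated in or follow directly from the article. Relaxing the level to one-sided 0.05, against the stated rule, still leaves power at 70%. This is not a detail left to a fuller document: the article makes a definite claim that its own figures contradict.

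**What to change.** Rewrite the power sentence in the Sample size section to state:

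- the formula and the one-sided 0.025 level;
- that 80% power for a margin of 1.3 needs about 456 deaths (457 rounded up);
- that 956 patients at 30% 12-month mortality are expected to give about 272 deaths and about 58% power (60% if dropout costs no deaths);
- as a labelled sensitivity only, power of about 47% and 39% if 12-month mortality were 23% or 18%.

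Add that pooled deaths, both arms together, will be tracked so that the achievable power can be restated without unblinding.

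An alternative is to state the true hazard ratio at which 956 patients do give 80%: about 0.93 with deaths held at 272, or about 0.92 once fewer deaths in the better arm are allowed for. This is weaker, because it replaces the explicit assumption of equal mortality with one chosen to fit the sample size, and it would need its own justification.

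The correction costs a rewording and a less favourable power figure. It needs no added patients and changes no procedure. If the sponsor wants 80% power under the stated assumptions, the requirement is about 1,604 patients.
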